**Figure 1 F1:**
[figure not shown]
Trial flow chart.

**Table 1 T1:** Study design schedule

**Period**	**Screening**	**Baseline**	**Treatment****(w1-6)**				**Follow**-**up****(w7-30)**							
**Week (W)**	***W-******1***	***W0***	***W2***	***W3***	***W4***	***W6***	***W15***	***W16***	***W17***	***W18***	***W27***	***W28***	***W29***	***W30***
Eligibility	X													
Informed consent	X													
Demography and medical history	X													
Physical examination	X													
Laboratory test	X													
1-h pad test		X	X			X								
72-h bladder diary		X	X		X	X	X	X	X	X	X	X	X	X
Weekly consumption of pads		X	X		X	X	X	X	X	X	X	X	X	X
Application of other treatments for SUI		X	X		X	X	X	X	X	X	X	X	X	X
ICIQ-UI Short form		X				X				X				X
Self-report assessment of therapeutic effect			X		X	X				X				X
Safety of EA			X		X	X								
Discomfort and acceptance of EA			X			X								
Assessment of blind method				X		X								
Adverse event			X			X	X	X	X	X	X	X	X	X
Compliance			X			X	X	X	X	X	X	X	X	X

### Ethics

The study is in accordance with the principles of the Declaration of Helsinki, and has been approved by the ethics committee boards of the participating hospitals (Ethics approval numbers: 2012EC007; 2013XL001-2; ECPJ-BDY-2013-04; 2013–033; 2013–7; TYLL2013; HN-LL-KY-2013-001-01; 2013EC001; HBZY2013-C007-01; 2013NL-013-04; 2013–02; 2012EC007) (Additional file 1). Written informed consent will be obtained from each subject before the patients enter the trial.

### Participants

The trial plans to recruit 500 women with pure SUI using research nurses or students majoring in acupuncture to do the recruiting.

Inclusion criteria are: (1) aged 40–75 years; (2) involuntary leakage of urine on effort, exertion, sneezing or coughing that stops when the stress ends [13]; (3) visible involuntary leakage from the urethra synchronous with increased abdominal pressure, or a pad weight gain >1 g in a 1-h pad test [13]; (4) no symptoms of urinary frequency and urgency; and (5) voluntarily join the research and sign the informed consent.

Exclusion criteria are: (1) urge urinary incontinence, mixed urinary incontinence, or overflow urinary incontinence; (2) having ever undergone an operation for urinary incontinence or on the pelvic floor; (3) female genital prolapse greater than degree 2; (4) symptomatic urinary tract infection; (5) residual urinary volume (RUV) > 30 mL; (6) maximum flow rate (Qmax) ≤20 mL/s; (7) limited in walking, stairs climbing and running; (8) receiving specific treatment for SUI, or taking medicine that may affect bladder function; (9) serious cardiovascular, cerebral, liver, kidney, or psychiatric disease, diabetes, multiple system atrophy, injury of cauda equina, or myeleterosis; (10) pregnancy or lactation; and (11) having a cardiac pacemaker, a metal allergy, or a severe needle phobia.

### Interventions

Acupuncture will be performed by registered acupuncturists with over 2 years of experience.

#### Treatment group

Acupuncture points (bilateral Zhongliao BL33 and Huiyang BL35) are selected based on evaluation of acupuncture literature, our pilot study and consensus of 10 Chinese acupuncture experts (Additional file 2). Before needling, sterile adhesive pads will be pasted onto the selected acupuncture points (for both groups, to ensure subject blinding). The adhesive pads (10 mm in diameter, 5 mm thick) are made of a special sponge and have a sticky side (Suzhou Medical Appliance Factory, China) (Additional file 3). The needles (0.30 mm in diameter, 75 mm in length, Hwato Brand, Suzhou Medical Appliance Factory, China) will be inserted at bilateral BL33 to a depth of 50–60 mm with an angle of 30-45° inward and downward. Bilateral BL35 are needled to a depth of 50–60 mm outward and upward slightly. Deqi, the needling sensations felt by a patient that indicates that the point has been stimulated, will be achieved by lifting, thrusting, and twirling the four needles evenly three times. The electric stimulators (SDZ-V electroacupuncture apparatus, Suzhou Medical Appliance Factory, China) will connect the bilateral BL33 points and the bilateral BL35 points and a continuous wave of 50 Hz frequency and an intensity of 1–5 mA will be applied. The intervention of treatment group is shown in Additional file 4.

#### Control group (sham EA)

Sham points, which are 1 cun lateral to BL33 and BL35, will be used to match each real point. Sham BL33 and BL35 will be needled through adhesive pads to the skin (for the fixation of needles) without penetrating the skin using blunt needles 0.30 mm in diameter, 25 mm in length (Hwato Brand, Suzhou Medical Appliance Factory, China). The needles will then be lifted, thrust, and twirled evenly three times to match the procedure undertaken for the treatment group. The sham electrode lines (Additional file 5), which look identical to the real ones but with the inner metal wire cut off, will be applied to bilateral sham BL33 and bilateral sham BL35, respectively, and a continuous wave of 50 Hz frequency and an intensity of 5 mA will be applied. When turned on, electric acupuncture apparatus looks normal but has no current output. The intervention of the control group is shown in Additional file 6.

For both groups, the needles will be retained for 30 min for each treatment session. The participants will be treated with EA three times a week, on alternate days, for six successive weeks; 18 sessions for each patient in total.

### Permitted and prohibited concomitant treatments

Throughout the trial, participants will be discouraged from undertaking any additional specific treatments for SUI including: medications such as duloxetine and imipramine; PFMT; feedback therapy; electrical or magnetic stimulation via pelvic floor, vagina or anus; and transcutaneous electrical nerve stimulation to the pelvic floor. For any unallowed treatment that has already been used, relevant information should be recorded in the patient’s case report form.

### Outcome measures

The primary outcome will be the change in the amount of urine leakage at week 6 from the baseline, measured by a 1-h pad test. The change at week 2 from the baseline will also be assessed. The 1-h pad test will be conducted based on the International Continence Society (ICS) guidelines [14] at the baseline, at week 2, and at week 6 (see Table 2). Secondary outcomes include seven items, the details of which are listed in Table 2.

**Table 2 T2:** Trial outcomes

**Primary outcome**	**Time point**
Change in amount of urine leakage at week 6 from the baseline measured by 1-h pad test	Evaluated at week 6
**Secondary outcomes**	
1. 72-h IEF	Evaluated at weeks 6, 18, and 30. The change of average 72-h IEF from the baseline will be analyzed
	Based on a 72-h bladder diary, the average 72-h IEF of week 6 is calculated by averaging the IEF of weeks 2, 4, and 6; values of week 18 and 30 are calculated by averaging IEF of weeks 15–18 and 27–30, respectively
2. ICIQ-UI Short Form score	Evaluated at weeks 6, 18, and 30. The change of score from the baseline will be analyzed
3. Severity of urinary incontinence	Evaluated at weeks 6, 18, and 30. Change in the number and percentage of severity rating from the baseline will be analyzed
	The most severe degree during weeks 2, 4, and 6 will be taken as severity of urinary incontinence of week 6
	The most severe degree during weeks 15–18 and weeks 27–30 will be taken as severity of urinary incontinence of week 18 and week 30, respectively
4. Self-report assessment of therapeutic effect	Evaluated at weeks 6, 18, and 30
	A 4-point scale is used: no help, little help, medium help, and great help
5. Weekly consumption of pads	Evaluated at weeks 6, 18, and 30. The change in average consumption of pads from the baseline will be analyzed
	The pads consumption of weeks 6, 18, and 30 will be calculated by averaging the weekly usage of pads during weeks 1–6, weeks 7–18, and weeks 19–30, respectively
6. Application of other treatment for SUI (including drugs and other specialist treatment)	Evaluated at weeks 6, 18, and 30. The number of patients who used other treatments for SUI during the trial will be analyzed between the two groups
7. Subgroup analysis stratified by incontinence severity	Evaluated at weeks 6, 18, and 30
	Stratified by incontinence severity at the baseline, the correlation between the rating of incontinence severity and the treatment effect will be analyzed. Different outcomes of treatment effect are used in each evaluation: week 6, the change in amount of urine leakage at week 6 from the baseline measured by 1-h pad test; week 18, the change of average 72-h IEF at week 18 from the baseline; and week 30, the change of average 72-h IEF at week 30 from the baseline

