**Methods/Design:**

This is a large-scale multicenter subject-blinded randomized controlled trial. A total of 500 women with pure stress urinary incontinence will be randomly assigned to two groups: a treatment group and a control group. The treatment group will receive electroacupuncture with deep needling at acupuncture points BL33 and BL35. The control group will receive sham electroacupuncture with non-penetrating needling at sham locations for the acupuncture points of BL33 and BL35. Participants will be given three sessions a week for 6 weeks. A 24-week-long follow-up will be conducted. The primary outcome will be the change in amount of urine leakage at the sixth week from a baseline measured by a 1-h pad test. The secondary outcomes include: the 72-h incontinence episode frequency based on a 72-h bladder diary; the score of International Consultation on Incontinence Questionnaire-Urinary Incontinence Short Form; the degree of urinary incontinence based on a 72-h bladder diary; self-assessment of the therapeutic effect; weekly consumption of pads; application of other treatments for stress urinary incontinence; and subgroup analysis stratified by incontinence severity. The safety of electroacupuncture will also be assessed.

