4. Analysis of efficiency: Intention-to-treat (ITT) analysis will be used to assess the validity of the study. Efficiency analysis will be based on the ITT population which is defined as all randomized participants. Missing data and non-compliance data will be included in the efficiency analysis. Missing data, from subjects without any treatment after randomization, or without any valid data of evaluation although treated, will be analyzed by multiple imputation by the inverse probability weighting method. Non-compliance data will be analyzed by the instrumental variable.

5. Analysis of primary outcome: In this study, we will use the change in the amount of urine leakage at week 6 from the baseline as the primary outcome. To adjust for baseline imbalance, a comparison of the decreased value of urine leakage between the groups will be done by ANCOVA using baseline and centers as covariates, when the residual are normally distributed. Meanwhile, a covariance model including interactions between centers and group will be made to analyze the center effect. Causes will be further analyzed if any center effect is identified. Comparison of decreased value of urine leakage between groups will be analyzed by a non-parametric test if the residual are abnormally distributed with neglect of baseline balance.

6. Analysis of secondary outcomes:

A 72-h incontinence episode frequency (IEF), the International Consultation on Incontinence Questionnaire-Urinary Incontinence (ICIQ-UI) Short Form score, and weekly consumption of pads of weeks 6, 18, and 30 will be compared with their respective baselines, and a *t*-test or non-parametric test will be used for comparison among groups.

For severity of urinary incontinence based on a 72-h bladder diary and a self-report assessment of therapeutic effect, the case number and percentage of each rank of weeks 6, 18, and 30 will be compared with their baselines, and a chi-square test or non-parametric test will be used for comparison among groups.

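### Follow-up severity is the worst of three or four diaries but its change is measured from one baseline diary, which biases the within-arm change towards worsening; the self-report scale has no baseline to be compared with

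*Protocol article*

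**What the plan says.** Severity is secondary outcome 3 in Table 2 of the protocol article. The abstract identifies it as "the degree of urinary incontinence based on a 72-h bladder diary".

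- **Week 6 (Table 2):** "The most severe degree during weeks 2, 4, and 6 will be taken as severity of urinary incontinence of week 6". That is three diaries.
- **Weeks 18 and 30 (Table 2):** "The most severe degree during weeks 15–18 and weeks 27–30 will be taken as severity of urinary incontinence of week 18 and week 30, respectively". That is four diaries each.
- **What is analysed (Table 2):** "Change in the number and percentage of severity rating from the baseline will be analyzed".
- **Baseline (Table 1):** the row "72-h bladder diary" is blank at W-1 and has one mark before treatment, at W0. No text gives baseline severity a multi-diary rule.
- **Analysis (Statistical analysis, item 6):** for severity and for the self-report assessment, in one sentence, "the case number and percentage of each rank of weeks 6, 18, and 30 will be compared with their baselines", followed by a comparison between groups.
- **Self-report scale:** Table 2, item 4, has four levels, from no help to great help. In Table 1 the row "Self-report assessment of therapeutic effect" is marked at W2, W4, W6, W18 and W30, and blank at W-1 and W0.

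**The concern.** The highest of several grades from one patient can only equal or exceed any one of them. Setting a maximum of three or four diaries against one diary therefore compares two different quantities. If nothing has changed, the follow-up grade still tends to come out higher. If the patient has improved, part or all of the improvement can disappear. At week 6 the rule also brings in the week-2 diary, when 6 of the 18 planned sessions (three a week for two weeks) have been given.

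The comparison with baseline is a planned analysis. The general part of the Statistical analysis section assigns non-parametric tests to categorical data compared with baseline, so a significant within-arm worsening could be reported that comes from the derivation alone.

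The self-report problem is separate and simpler. A scale that asks how much treatment helped has no value before treatment starts, so one of the stated comparisons cannot be carried out.

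**Working it through.** The article attaches no figure to either outcome, so there is nothing of its own to reproduce. It also gives no number of grades, cut points or between-diary correlation. These are assumed below and varied.

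**Inputs from the documents.** Baseline diaries: 1 (Table 1). Follow-up diaries: k = 3 at week 6, k = 4 at weeks 18 and 30 (Table 2). Patients per arm: 250 (Sample size calculation). Test level: 0.05 two-sided (Statistical analysis).

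**Assumed model.** Latent severity on diary j is √ρ·u + √(1−ρ)·e_j, with u and e_j standard normal, cut into equally frequent grades, with no true change. Baseline grade is B = G_0. Follow-up grade is F = max(G_1, …, G_k). The shares P(F > B) and P(F < B) come from 400,000 simulated patients per setting.

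**Result with four grades, shown as worse / better:**

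| Correlation ρ | One diary v one | Worst of 3 (week 6) | Worst of 4 (weeks 18, 30) |
|---|---|---|---|
| 0.5 | 31% / 31% | 52% / 11% | 56% / 8% |
| 0.7 | 26% / 26% | 45% / 9% | 49% / 7% |
| 0.8 | 23% / 23% | 40% / 8% | 44% / 6% |
| 0.9 | 18% / 18% | 31% / 6% | 35% / 4% |
| 1.0 | 0 / 0 | 0 / 0 | 0 / 0 |

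At ρ = 0.8 the mean change is +0.40 grade for k = 3 and +0.48 for k = 4. The share in the top grade goes from 25% at baseline to 38% and 41%. With three grades and k = 3, the shares run from 23% / 4% (ρ = 0.9) to 44% / 9% (ρ = 0.5).

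**Tests under no true change.** In 1,000 simulated trials with 250 per arm, four grades and k = 3, the within-arm signed-rank test rejected in 100% of trials at ρ = 0.7, 0.8 and 0.9. The between-arm Mann–Whitney test of follow-up grades rejected in 6.3%, 4.6% and 5.3%, close to its nominal 5%.

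**A growing true effect.** Assume improvement of 0.2, 0.4 and 0.6 SD at weeks 2, 4 and 6 in the treated arm and none in control, with four grades and ρ from 0.7 to 0.9. The week-6 diary alone shows a change of about −0.6 grade in the treated arm. The worst-of-three rule shows between −0.09 and +0.10. The between-arm difference falls from about 0.59 to 0.37–0.39 grade.

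**Self-report.** No arithmetic applies. Item 6 calls for a baseline comparison, Table 1 first schedules the scale at W2, and the response levels presuppose treatment. These cannot all hold.

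**The case against.** The strongest reply is that the trial's question is electroacupuncture against sham. The same worst-grade rule applies in both arms, and item 6 also plans a comparison between groups. Worst grade in a period is a prespecified and cautious summary: it works against showing improvement, not in favour of the active arm. This largely stands. A reader might infer that the randomised comparison of severity is biased, but the documents do not support that. Under the null it keeps its size when diary return is equal. Fewer returned diaries lower the expected maximum, so unequal return could create a difference, but nothing in the article suggests that return will differ. What remains for the between-arm comparison is dilution at week 6 if the effect grows over time.

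A reader might also argue that the worst of three diaries exceeds one baseline diary with probability 75%, and the worst of four with 80%. Those figures require that no two diaries tie. Severity is a graded rating in which ties are common, so they do not apply.

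A third inference is a spurious decline between week 6 and weeks 18 and 30. The step from three to four diaries does add a little (0.40 to 0.48 grade at ρ = 0.8), but the article plans no comparison between those times.

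On self-report, Table 2 lists only evaluation times for item 4, with no change from baseline. The joint sentence in item 6 therefore reads as a drafting slip. It is minor, but as written it specifies an analysis that cannot be run.

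**Conclusion.** The point holds for the within-arm change from baseline in severity. Its direction follows from the definitions alone and fails only if every patient's grade is constant across diaries. Its size rests on the assumed latent normal model, four equal grades and correlation of 0.5 to 0.9. No single row of the table should be read as a prediction for this trial.

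The self-report comparison with baseline contradicts the schedule and the scale itself. Both matters concern secondary outcomes and should be corrected. Neither affects the primary 1-h pad test analysis.

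**What to change.** 1. For change from baseline, grade severity from one diary at each time: the W6, W18 and W30 diaries, each against W0.
2. If the worst-grade summary is kept, use it only for the comparison between arms, and say so in Table 2 and item 6.
3. In item 6, remove the self-report assessment from the comparison with baseline and compare arms only at weeks 6, 18 and 30.

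Grading the averaged 72-h incontinence episode frequency would remove most of the shift. It still sets three or four diaries against one and includes week 2, so it is not strictly like for like.

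The cost is wording and derivation only, since every diary needed is already scheduled. The drawback is that a single diary is somewhat noisier than a multi-diary summary.

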#### Statistical analysis

Statistical analysis will be performed by the Clinical Evaluation Center of CACMS in Beijing and the Department of Biostatistics, University of Washington, Seattle, United States. The statistician will be blinded from the allocation of groups. PASW Statistics 20.0 and SAS9.0 statistical software will be used for data analysis. The level of significance is established at α<0.05 with a two-tailed test.

The main objective is to compare the change in the amount of urine leakage at week 6 from the baseline between the treatment group and the control group. The null hypothesis is that the treatment group has the same change as the control group, while the alternative hypothesis is that the treatment group shows a greater decrease.

Continuous data will be represented by the average, standard deviation, median, minimum value, and maximum value, whereas categorical data will be represented by percentages. For comparison with the baseline, a *t*-test or non-parametric test will be used for continuous data, and non-parametric tests for categorical data. For comparison of two independent samples: if the residual are normally distributed, the analysis of covariance (ANCOVA) will be used for the primary outcome and subgroup analysis stratified by incontinence severity, a *t*-test for other continuous data, and a chi-square test for categorical data; if the residual are abnormally distributed, a non-parametric test will be used for both continuous and categorical date. Detailed contents and methods are as follows.

1. Case distribution and compliance analysis: The case distribution of both groups in every center will be described. The total drop-out rate and the drop-out rate due to adverse events, of both groups, will be compared using Fisher’s exact test.

2. Analysis of baseline characteristics.

3. Analysis of compliance: The implementation of protocol intervention will be compared between the two groups. Compliance will be evaluated according to the case report forms.

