Although we will exclude patients already receiving some form of treatment for SUI at the trial outset and will discourage participants from taking additional treatments during the trial period, we anticipate that some patients will not adhere to this. In these instances the patients will record the treatments received and/or medications taken and the number of patients and treatment sessions of the treatment period and two follow-up periods will be described, and chi-square tests or non-parametric tests will be used for comparison among groups.

To assess the effect of EA for different degrees of SUI, subgroup analysis will be stratified by incontinence severity measured by a 1-h pad test at the baseline. In comparison among the groups, changes in the amount of urine leakage at week 6 from the baseline will be analyzed by ANCOVA or nonparametric tests. Changes in the 72-h IEF at weeks 18 and 30 will be analyzed by covariance analysis, non-parametric tests, or longitudinal data model.

7. Analysis of safety: Adverse events will be listed and analyzed using a chi-square test or Fisher’s exact test. Severe adverse events should be listed in detail. EA-related adverse events are to be listed in detail and compared among groups.

8. Analysis of blind method: The number and percentage of subjects choosing true EA in the selected two centers will be established. A chi-square test or non-parametric test will be used for comparison among groups.

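### The week-6 correlation of baseline severity with change from baseline is coupled through the shared pad test, and no arm-by-severity interaction is named to answer the subgroup question

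*Protocol article*

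**What the plan says.** Table 2 of the protocol article lists a subgroup analysis by baseline severity as secondary outcome 7 and says that "the correlation between the rating of incontinence severity and the treatment effect will be analyzed". It then names the variable that stands for the treatment effect at each visit:

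- Week 6: "week 6, the change in amount of urine leakage at week 6 from the baseline measured by 1-h pad test".
- Week 18, and likewise week 30: "week 18, the change of average 72-h IEF at week 18 from the baseline".

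These are patient-level changes from baseline, not differences between EA and sham.

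Item 6 of the Statistical analysis section fixes the stratifying measurement: "subgroup analysis will be stratified by incontinence severity measured by a 1-h pad test at the baseline". It also names the tests. For week 6, "In comparison among the groups, changes in the amount of urine leakage at week 6 from the baseline will be analyzed by ANCOVA", with non-parametric tests as the alternative. For the later visits, "Changes in the 72-h IEF at weeks 18 and 30 will be analyzed by covariance analysis, non-parametric tests, or longitudinal data model". The general paragraph of that section, on comparing two independent samples, says that if residuals are normal "the analysis of covariance (ANCOVA) will be used for the primary outcome and subgroup analysis stratified by incontinence severity".

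The only interaction in the article is in item 5, for the primary outcome: "a covariance model including interactions between centers and group will be made to analyze the center effect".

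The Sample size calculation section gives the planned subgroup analysis as one of two reasons for raising the total from 280 to 500.

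**The concern.** At week 6 the baseline pad weight sets the severity rating and is also the starting point of the change score. A woman whose baseline reading was high by chance is graded as more severe and, on average, shows a larger fall at the next test, whatever she received. Their correlation therefore mixes regression to the mean with any real effect, and it contains no comparison with sham. The trial exists to separate a therapeutic effect from a placebo effect, and this quantity cannot do so.

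The planned comparisons of EA with sham by stratum do use the randomisation. But whether EA works differently in mild and severe incontinence is a question about the difference between stratum effects, and no test or estimate of that difference is named. At stake is a listed secondary outcome that helped to justify 220 additional participants (500 − 280).

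**Working it through.** **Inputs from the protocol article.** SD of change 2.61 g, difference to detect 1 g, predicted drop-out 20%, 250 per arm, two-sided 5% for analysis.

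**Assumptions.** The article does not give the baseline to week-6 correlation r of pad weight, so it is varied from 0.3 to 0.9. Variances at baseline and week 6 are taken as equal. Severity cut-points are not given, so thirds of the baseline distribution are used.

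**The plan's own figure.** Pooled pilot SD = √((2.26² + 0.97²)/2) = 1.74, and × 1.5 = 2.61. One-tailed n = 2 × (1.645 + 1.282)² × 2.61² / 1² ≈ 117 per group, as stated.

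**Week-6 coupling with no EA effect.** Let B be baseline, F week 6, common variance σ², and decrease D = B − F.

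- Cov(B, D) = σ²(1 − r)
- Var(D) = 2σ²(1 − r)
- corr(B, D) = √((1 − r)/2)

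Grouping B into thirds weakens this slightly. A simulation (250 per arm, 3,000 runs per r, Spearman correlation) gave:

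| r | formula, continuous B | thirds, EA | thirds, sham | significant and positive, EA |
|---|---|---|---|---|
| 0.3 | 0.59 | 0.53 | 0.53 | 100% |
| 0.5 | 0.50 | 0.44 | 0.44 | 100% |
| 0.7 | 0.39 | 0.34 | 0.34 | 100% |
| 0.8 | 0.32 | 0.28 | 0.28 | 99% |
| 0.9 | 0.22 | 0.20 | 0.19 | 88% |

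With log-normal data (r = 0.5, 0.7 and 0.9) the correlation in the EA arm was significant and positive in 78–100% of runs.

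**The artefact cancels between arms.** At r = 0.5 the mean decrease in the severe third was 1.42 g in each arm. In the mild third it was −1.42 g (EA) and −1.41 g (sham). The severe-minus-mild difference in the EA–sham contrast was about 0.

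**EA against sham by stratum, no EA effect.** Rejection was 4.5–5.9% per stratum. At least one of three strata rejected in 14–15% of runs (theory: 1 − 0.95³ = 14.3%). The pattern of the severe stratum favouring EA and the mild stratum not significant occurred in 2.2–2.8%.

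**Weeks 18 and 30.** With severity by pad test and outcome by change in incontinence episode frequency (IEF), the correlation was about 0 and was significantly positive in 1.6–3.1% of runs. This assumes independent measurement errors in the two instruments.

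**What an interaction does.** The baseline-adjusted severe-minus-mild contrast in the EA–sham effect had a two-sided false-positive rate of 4.9–5.7%.

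**What an interaction can detect.** Evaluable per arm = 250 × 0.8 = 200. With two equal strata there are 100 per arm in each.

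- SE of one stratum effect = 2.61 × √(2/100) = 0.369 g
- SE of the difference between strata = √2 × 0.369 = 0.522 g
- Detectable with 80% power = 2.80 × 0.522 = 1.46 g

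This uses the unadjusted SD of change, so baseline adjustment would lower the figure somewhat.

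**Why differing stratum p-values are not evidence.** Suppose instead that EA has a true and uniform 1 g effect. In the same two-stratum setting, power is 77% in each stratum, so the two disagree on significance in 2 × 0.773 × 0.227 = 35% of trials although the effect is identical. This illustrates the missing interaction and is separate from the week-6 artefact.

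**The case against.** A reader might infer that the subgroup analysis will find EA better in severe incontinence even if EA does nothing. The documents do not support that. The tests named in the Statistical analysis section compare EA with sham. Regression to the mean is equal in randomised arms and drops out of that comparison, and the severe-only pattern appears in only 2–3% of null trials. The correlation is just as large under sham, so it becomes a false claim about EA only if someone reads it as an EA effect without looking at sham. The article does not say that this will be done.

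Three further objections deserve an answer.

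- *Correlation may be loose wording for relationship, since the Statistical analysis section names no correlation coefficient.* This is possible, but Table 2 states the correlation as the analysis and labels a change from baseline as the treatment effect. If a between-arm comparison is meant, the text should say so.
- *The coupling does not cover all visits.* This stands. It applies exactly to week 6. Weeks 18 and 30 use IEF, while severity is graded by the pad test.
- *An interaction term is a model detail that an article may leave to an analysis plan that is not shown.* Taken alone, its absence would not be a finding. The point is that the article does state a method for this question, and that method cannot answer it.

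It also stands that the primary analysis is untouched.

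**Conclusion.** The concern holds in limited form. At week 6 the stated correlation is positive in both arms without any EA effect, at about 0.2 to 0.5 for r between 0.9 and 0.3, and would usually be statistically significant. It therefore carries no information on whether the EA effect varies with severity. The sizes rest on the assumed r, equal variances and severity in thirds; the direction follows from the shared baseline.

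The stratum comparisons of EA with sham are valid as tests within each stratum, at about 5% error each. Without an arm-by-severity interaction, however, a difference between their results would not establish effect modification. The change is worth making because the analysis is a listed secondary outcome and helped to justify the enlarged sample.

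**What to change.** In Table 2, secondary outcome 7, and in item 6 of the Statistical analysis section, replace the correlation with one model per time point:

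- Week 6: ANCOVA of change in pad weight on arm, continuous baseline pad weight, centre, severity stratum and the arm-by-severity interaction.
- Weeks 18 and 30: the same form for change in 72-h IEF, adjusted for baseline IEF.

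Report the interaction estimate with its 95% CI, and the EA–sham estimate with CI in each stratum. Base any statement that the effect differs by severity on the interaction, not on which strata reach significance.

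The cost is analysis wording only; no data collection changes. The small downside is that fewer subgroup claims will be possible. Under the assumptions shown, the interaction detectable with 80% power is about 1.5 g, which exceeds the 1 g overall difference used to size the trial. The plan should say so.
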